## Background

Randomized clinical trials (RCTs) are the cornerstone of reliable evaluation of interventions in health care, with results that often impact clinical guidelines and evidence-based practice ultimately leading to better health care for patients [1–3]. However, conducting high-quality RCTs is challenging, resource intense, and associated with high costs [4, 5]. Tens of billions of dollars of public and private money are invested in RCTs every year, estimated to reach $68.9 billion a year by 2025 [6]. Moreover, RCT costs are rising. Over the last decade, a number of new initiatives and regulations were implemented to increase participant protection and to improve research quality [2, 7–10]. As a consequence, the complexity and administrative burden of RCTs have increased overall costs [11–15]. Furthermore, the implementation of medical advances, while highly desirable, has limited the incremental impact of new therapies, resulting in smaller beneficial effects of interventions, which requires larger RCT sample sizes [16, 17]. All these developments have resulted in escalating RCT costs, thus exasperating the problem of scarce resources for academic clinical research.

One consequence of these cost pressures is that the number of independent investigator-initiated RCTs has remained constrained over the last two decades [2, 18, 19] and a substantial proportion of these trials are prematurely discontinued due to recruitment and organizational problems [19], which risks many clinical research questions remaining unaddressed. Therefore, efforts to make investigator-initiated RCTs more cost-effective and sufficiently funded are urgently needed.

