### Eligibility criteria and trial identification

RCTs will be included if they have been completed or are close to completion (statistical analysis ongoing or manuscript in preparation). Trials will be excluded if they are industry sponsored, dose-finding RCTs, RCTs primarily evaluating pharmacokinetics or physiology, include healthy volunteers, or RCTs that published results more than 10 years prior to the start of this investigation. To enhance comparability across countries, we will aim to include 10–15 RCTs each from cardiovascular, oncology, surgical, and miscellaneous fields. However, it was challenging to find principal investigators willing to share their cost data, as such we decided to expand our scope and include a small sample of pilot studies (*n* = 10) and RCTs initiated in Switzerland but conducted in low- and lower-middle-income countries (*n* = 10).

We will identify potentially eligible RCTs using two approaches: Firstly, we will use a convenience sample and contact Clinical Trial Units (CTUs), trial networks, and individual principal investigators known to the authors in all three countries and ask them about eligible investigator-initiated RCTs they could contribute. Most of our direct trialist connections are in Switzerland. In particular, we will approach the Swiss CTU network; the KKS Network, UK Registered CTUs Network; Network of Hubs for Trials Methodology Research (UK); UK Trial Managers’ Network, Trial Forge Initiative (UK); Koordinierungszentren für Klinische Studien Network (DE); Oncology network (DE); and the Clinical Trials Centre Cologne (DE).

Secondly, we will screen trial registries for completed RCTs and then invite principal investigators to participate in our study. These trial registries will include clinictrials.gov, the ISRCTN registry, the Health Research Authority (NHS) registry, Kofam (Swiss Clinical trial registry), and the Deutsches Register Klinischer Studien (DRKS; the German clinical trial registry).

For each RCT contributed to the project, we will offer the trial teams 200 euros as a compensation for their efforts.

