### Statistical analysis

We will calculate proportional contributions to total costs for individual cost items and for the three pre-defined study phases (preparation, conduct, and finalization). Proportions across RCTs will be summarized with descriptive statistics accompanied by 95% CIs. We will summarize total resource use (working hours and costs), as well as resource use and costs for individual cost items, and costs per patient using descriptive statistics (means or medians accompanied by standard deviations (SDs) or 25th to 75th percentile ranges [IQRs] according to the distribution, minimum [min] and maximum [max], respectively) overall and stratified by RCT over- or under-budget (± 10%), medical field, intervention type, country, and pilot vs non-pilot RCTs (objectives A–D).

We will categorize reasons for going over- or under-budget as reported by trial investigators and reasons for prolongation of recruitment [43] (objective C). In sensitivity analyses, we will calculate results without adding 30% of unaccounted time and/or adding overhead costs. We will not exclude any collected data from planned analyses. Outliers will be reviewed and checked/verified with principal investigators of included trials.

We will conduct two multivariable linear regression analyses with total costs in US dollars and total costs per patient as dependent variables [44]. Medical field, country, number of trial sites, actual sample size (only in regression model for total costs), routine data use, intervention type, and actual trial duration will be used as independent variables in both regression analyses. As for the investigation into the strata of cost proportions of RCTs across medical fields, intervention types, and countries, we will first plot distributions of cost proportions graphically stratified by medical field, intervention type, and country. For each RCT, we will descriptively compare the originally planned versus actual total costs, the originally planned versus actual recruitment duration, and the planned versus actual sample size (objective C).

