We will calculate excess costs for each RCT (delta of originally planned total costs and actual total costs [Total costs − Planned Costs]). This will help investigate trial characteristics associated with excess costs of an RCT (dependent variable). We will develop a multivariable regression model with delta in recruitment duration, actual sample size, and actual number of trial sites, country, intervention type, and medical field as independent variables (objective C).

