#### Changes to the original OSF registration

In our initial OSF registration, we had planned to include an additional sample of Canadian RCTs. Due to feasibility issues in Canada and lack of support from collaborators, we needed to exclude the country. Furthermore, it was challenging to find principal investigators willing to share their cost data, as such we decided to expand our scope and include a small sample of pilot studies (*n* = 10) and RCTs initiated in Switzerland but conducted in low- and lower-middle-income countries (*n* = 10). In addition, we initially did not want to include trials published later than 5 years; this was extended to 10 years to increase our sample of eligible RCTs.

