As a major strength, this study will be the first of its kind to use activity-based costing to systematically and empirically investigate the resource use and costs of RCTs in Germany, Switzerland, and the UK. However, the study also has limitations. Firstly, despite including trials from different medical fields and countries, our findings may not be generalizable to all types of trials or research settings, as the costs can vary widely depending on the research question, therapeutic area, and location. Secondly, we will collect self-reported retrospective data from investigators and their teams, which may introduce reporting bias and inaccuracies. Especially the variable costs (time expenditures) are not usually recorded on site and need to be estimated by the principal investigator and study team members. Thirdly, RCTs of principal investigators who agreed to share the resource use and cost data with us might not be representative of all RCTs, but could be a selection of more successful RCTs compared with those for which principal investigators did not share cost data. We will keep a list of all contacted trial investigators, who do not wish to participate in our study, and will extract characteristics of corresponding not-included RCTs from trial registries and publications to enable a comparison of RCT characteristics. Fourth, our sample only includes trials conducted in Europe and costs may differ in North America or Asia because of differences in healthcare systems, medical research, and health insurance policies. Lastly, our research does not investigate if the different monitoring strategies have an influence on data quality.

Future research should consider alternative methodologies such as prospective data collection to provide more accurate cost estimates.

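### Apart from currency and inflation conversion, no analysis accounts for when a trial ran, although the eligibility window now spans ten years of publications

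*Protocol article*

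**What the plan says.** **Window.** Under Eligibility criteria and trial identification, the article excludes "RCTs that published results more than 10 years prior to the start of this investigation". The section on changes to the OSF registration explains that the limit had been 5 years and that "this was extended to 10 years to increase our sample of eligible RCTs".

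**Trend.** The Background states "Moreover, RCT costs are rising" and, after describing initiatives and regulations of the last decade, says that "the complexity and administrative burden of RCTs have increased overall costs".

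**How time use is obtained.** The Discussion says that staff time expenditures "are not usually recorded on site and need to be estimated by the principal investigator and study team members".

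**Models.** Under Statistical analysis, the total-cost and cost-per-patient regressions use medical field, country, number of sites, sample size (total-cost model only) and then "routine data use, intervention type, and actual trial duration will be used as independent variables in both regression analyses". The excess-cost model uses "delta in recruitment duration, actual sample size, and actual number of trial sites, country, intervention type, and medical field as independent variables".

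**Strata and sensitivity analyses.** Descriptive summaries are given overall and "stratified by RCT over- or under-budget (± 10%), medical field, intervention type, country, and pilot vs non-pilot RCTs". The sensitivity analyses concern only the 30% uplift for unaccounted time and the overhead.

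**Calendar handling that exists.** Under Data management, costs are converted to US dollars at the exchange rate of the recruitment start date and inflated to 2022 with the World Bank index.

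**The concern.** The Background describes a trend made up partly of extra work: more approvals, more documentation, more administration. A general price index puts old and new trials on the same price level, but it does not add the tasks that an older trial never had to perform. If trials from one country or field are on average older, the coefficient for that group absorbs part of the era difference. The cost models contain nothing that could separate the two, because trial duration is a length and not a date.

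Two uses of the results are affected. The first is the comparison across countries, fields and intervention types (objective B, and hypothesis iv on similar cost structures and fixed items). The second is the use of pooled figures to plan future trials, which the Discussion names as a purpose. Even with perfect balance between groups, a pooled average covers a period over which the protocol says that burden grew.

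**Working it through.** The plan gives no figure on this point, so there is none to reproduce. The check has two parts.

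**1. Is there a calendar term anywhere?**

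| Element | Calendar term? |
|---|---|
| Total-cost model | No |
| Cost-per-patient model | No |
| Excess-cost model | No; it has the change in recruitment duration, which is a length |
| Descriptive strata | No |
| Sensitivity analyses | No; unaccounted time and overhead only |
| Data management | Yes, for prices: dated exchange rate and inflation to 2022 |

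The price steps do not reach everything. Working hours are summarised as a result in their own right and are not price-adjusted. If one dated factor is applied to all costs of a trial, it cancels from numerator and denominator of a cost share, so shares are left as they were.

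**2. How large could the residual be?**

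Inputs, both assumed because the documents give neither:
- g, real cost growth per year above general inflation: 1% to 5%.
- d, difference between two groups in mean recruitment-start year: 2 to 5 years, with 0 as the balanced case.

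Formula: spurious relative difference = (1 + g)^d − 1.

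| g | d = 0 | d = 2 | d = 5 |
|---|---|---|---|
| 1% | 0 | 1.01² − 1 = 2.0% | 1.01⁵ − 1 = 5.1% |
| 2% | 0 | 1.02² − 1 = 4.0% | 1.02⁵ − 1 = 10.4% |
| 3% | 0 | 1.03² − 1 = 6.1% | 1.03⁵ − 1 = 15.9% |
| 5% | 0 | 1.05² − 1 = 10.3% | 1.05⁵ − 1 = 27.6% |

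The table concerns total costs. Growth that is uniform across items would leave cost shares unchanged. Shares move only if burden rose unevenly, for instance more in approvals than in treatment visits, and nothing in the documents allows that to be sized.

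**The case against.** The strongest case against the point runs as follows.

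- **Nothing is misstated.** The aim is descriptive and exploratory, and the regressions report associations. This stands: the point is about a better analysis choice, not a mistake. It is still not mere detail left to another document, because the article spells out its covariates, strata and sensitivity analyses.
- **Calendar time is not ignored.** The dated exchange rate and the inflation step handle general price change. This stands, and the concern is limited to what remains after them.
- **Part of the trend is already modelled.** The Background also blames larger sample sizes, and the models contain sites, duration and (for total cost) sample size. This stands; only growth in work for a given design is left.
- **The excess-cost model is a weak target.** Planned and actual costs come from the same trial, so burden foreseen at budgeting enters both. This stands.
- **The effect may be small against the noise.** As a rough proxy, the industry phase III quartiles in the Background (US$ 9 and 44 million) give a log-SD of ln(44/9)/(2 × 0.6745) = 1.18. Comparing 60 with 20 trials, 1.96 × 1.18 × √(1/60 + 1/20) = 0.60, a 95% interval of about 0.55 to 1.81 times the estimate. If covariates explain 40% of the variance, it is about 0.63 to 1.59. This stands as perspective. Imprecision does not remove a bias, however, and the pooled summaries do not depend on this contrast.

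A reader might infer that country and field effects *are* mixed with era. The documents do not show this, because they give no start years by group, and recruiting through volunteers and personal contacts does not by itself make trial age differ by country. A reader might also infer that recall error grows with the age of the trial. The article says that times must be estimated, but not that error increases with elapsed time, and it gives no direction of bias. It also provides for an interview and a cost report reviewed by the trial team.

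**Conclusion.** The point holds conditionally. After price conversion, nothing in the stated analysis accounts for when a trial ran, while the protocol itself describes a decade of growing burden and doubled the publication window. Country, field and intervention-type associations in the total-cost and cost-per-patient models could be confounded by era **if** trial age differs between these groups, and pooled summaries may lag behind current resource use.

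The size rests entirely on the two assumed inputs: zero under balance, and about 2% to 28% in the range shown. The excess-cost model is less exposed. The change is worth making because it is cheap and lets readers see whether the condition is met, not because the plan contains an error.

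**What to change.** 1. Add calendar year of recruitment start as a linear covariate in the total-cost and cost-per-patient regressions. It is optional in the excess-cost model.
2. Tabulate start year by country and by medical field, so that any imbalance is visible.
3. Repeat the main total-cost and cost-share summaries as a sensitivity analysis restricted to trials that meet the registered 5-year limit, and say whether the conclusions hold. The full-sample analysis stays primary, so the commitment not to exclude collected data from the planned analyses is kept.

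**Cost.** No new data are needed, because the recruitment start date is already required for the currency conversion. Each model loses one degree of freedom. The 5-year subset will be less precise, most of all for Germany and the UK with a target of 20 trials each. Start year also indexes time since conduct, so it cannot separate era from recall; its coefficient should be reported as the combined effect of both.

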## Study objectives and hypotheses

The aim of this study is to generate a database of detailed empirical resource use and cost data from 100 investigator-initiated RCTs in Switzerland, Germany, and the UK, so that we can descriptively investigate total RCT costs and proportions of total costs for individual cost items to achieve the following specific objectives:A)To investigate cost patterns on an absolute (actual costs in USD) and relative scale (% of total costs) including largest cost items for the whole RCT and for the planning, conduct, and finalization phases.B)To explore RCT costs across different strata including medical fields, intervention types, multicenter/single center status, and countries.C)To examine planned versus actual RCT costs and to explore factors that explain excess costs.D)To explore hidden costs associated with conducting an RCT such as resource use and costs for writing the protocol, trial committees, ongoing communication, and managing serious adverse events (SAEs).

We have the following specific hypotheses:(i)The expenses for participant recruitment and follow-up typically constitute the largest proportion of total RCT costs.(ii)Data monitoring constitutes—on average—less than 15% of total RCT costs.(iii)Delays in recruitment of trial participants explains most of the excess costs.(iv)Cost structures (proportions) and fixed cost items (e.g., regulatory or ethics committee approval) are similar across medical fields and countries.

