**Variable Costs (in days)** • Research protocol • Budget development • Grants and funding • Application EC, • Patient-related forms • Investigational brochure • Site-specific set-up Staff training • Acquiring study drug • Statistical analysis plan • Data management plan • Monitoring plan • Initial monitoring Visit • Biobank preparation • Communication funders and authorities • Communication involved sites • Communication other stakeholders • Communication patient representatives	**Variable Costs (in days or minutes)** • Screening • Informed consent and patient specific documents • Randomization • Baseline visit • Treatment: intervention • Treatment: control • Sample processing/analysis • Source data and data entry AEs, SAEs and SUSARs • Follow-up/Endline visit(s): • Ongoing communication • Upkeep of documentation • staff training /re-training • Amendments • Audits/ inspections • statistical services • Data management • Monitoring - Upkeep of biobank	**Variable Costs (in days)** • Data cleaning and database lock • Biospecimen storage/destruction • Statistical analyses • Final reporting • Manuscript • Other results dissemination

*Abbreviations*: *AE* adverse event, *SAE* serious adverse event, *SUSAR* serious unexpected serious adverse event, *EC* ethics committee

In short, we will be collecting two types of cost data: Firstly, the fixed costs associated with the trial, which are costs that are independent of time and human resources, such as ethical approval fees, insurance fees, travel costs, and material fees (Table 1). Secondly, we will be collecting variable costs, using a predefined list of study tasks, which are dependent on human resources, time expenditure of the team and salary, such as days needed to write the protocol, days for communication amongst stakeholders, minutes needed for patient screening, recruitment, and treatment (Table 1). Variable costs will be recorded in days or minutes for each study task, for each type of trial team member (principal investigator, site investigator, study nurse/coordinator, senior medical staff, junior medical staff, administrative staff, statistician, IT support and data management, monitor, laboratory staff, or others) and will then be multiplied by their gross yearly income (given by the study team) to calculate billable hours/days. The costs can be entered in five currencies: euro (€), Swiss franc (CHF), pound (£), and US dollar (USD).

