From protocols and publications, we will extract the relevant RCT baseline characteristics. These will include medical field (indication), type of intervention and control group, use of placebo, number of arms, type of patient population, specific trial design (e.g., cross-over or factorial design), number of trial arms, number of trial sites, planned and achieved sample size, originally planned total costs and planned budget (if available), primary outcome(s), trial duration, planned and actual recruitment duration, monitoring method, electronic or paper-based data capture/case report forms, and funding sources.

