#### Missing data

Throughout the study we will be in direct contact will principal investigators and all data entry will be followed by a detailed cost report and interview. As such, we do not anticipate missing data. Nevertheless, some investigators may not have calculated an initial budget for their trials, i.e., in these cases we will document missing budgets and for analyses in which initial budgets are considered we will conduct complete case analyses. If income was not provided by the institution to calculate billable hours, we will impute the median income for the respective country, for each specific team role.

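### The excess-cost model sets a cost difference and a recruitment-duration difference against sample size at its actual level only, so departure from planned enrolment is unadjusted and can bias the delay coefficient in either direction

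*Protocol article*

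**What the plan says.** Hypothesis (iii), in Study objectives and hypotheses, reads: "Delays in recruitment of trial participants explains most of the excess costs". In Statistical analysis, excess cost is defined for each trial as the "delta of originally planned total costs and actual total costs", calculated as actual minus planned. The model for it is then specified: "We will develop a multivariable regression model with delta in recruitment duration, actual sample size, and actual number of trial sites", with country, intervention type and medical field as the other independent variables.

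Two quantities are therefore differences from plan (cost and recruitment duration), and two are levels (sample size and number of sites). Data collection procedures lists "planned and achieved sample size" among the items extracted for every trial, so the departure from planned enrolment will be known. Statistical analysis uses planned against actual sample size only in a descriptive comparison for each trial. The same section adds a second source of evidence: "We will categorize reasons for going over- or under-budget as reported by trial investigators".

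**The concern.** The cost items include per-patient staff time, for example "minutes needed for patient screening, recruitment, and treatment". Actual cost therefore falls when fewer patients are enrolled than the budget assumed, and rises when more are. That effect depends on actual minus planned enrolment, which actual enrolment does not reveal. Two trials may each enrol 300 patients, one against a plan of 300 and the other against a plan of 330. At an assumed 4,000 USD per patient the second saves 30 × 4,000 = 120,000 USD against its budget. At an assumed 6,000 USD per month, that offsets 120,000 / 6,000 = 20 months of delay. The planned model cannot tell these two trials apart.

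Where missing patients and delay are correlated across trials, the delay coefficient takes up part of the enrolment effect. The coefficient could then count against hypothesis (iii) when delay does drive cost, or exaggerate its support.

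**Working it through.** **No figure to reproduce.** The protocol gives no numerical result or assumption for this model. The monthly cost of delay (c_T), the cost per patient (c_N) and the link between delay and shortfall below are all assumptions.

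**Formula.** Let D be delay in months, S = planned minus actual sample size, and excess cost = c_T·D − c_N·S + noise. If the model contains D and actual sample size but not S, the expected delay coefficient is

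c_T − c_N·g,

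where g is the coefficient of D when S is regressed on D and actual sample size: the extra patients missing per month of delay at a given actual size. The sign reverses when c_N·g exceeds c_T. There is no bias when g = 0, and delay is overstated when g is negative.

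**Set A.** 2,000 datasets of 80 trials. Planned size is lognormal (median 250, log-SD 0.8). Delay is 12 × difficulty plus a normal term with mean 6 and SD 6 months. The achieved fraction is 1 − 0.2 × max(difficulty, 0), plus a normal term with SD 0.05. Noise has SD 10% of planned cost, c_T = 6,000 USD, and only delay and the size term are fitted. One latent difficulty drives both variables, so the delay-shortfall correlation is about 0.70 and g = 2.40.

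| Correlation | USD per patient | c_T − c_N·g | Simulated, actual size in model |
|---|---|---|---|
| 0.7 | 1,000 | 6,000 − 2,400 = 3,600 | about 3,600 |
| 0.7 | 2,000 | 6,000 − 4,800 = 1,200 | about 1,200 |
| 0.7 | 4,000 | 6,000 − 9,600 = −3,600 | −3,500 to −3,600 (negative in 88%) |
| 0 | 4,000 | 6,000 | 6,000 to 6,200 |
| −0.4 | 4,000 | 6,000 + 5,400 = 11,400 (g = −1.35) | about 11,400 |

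Reversal at correlation 0.7 needs more than 6,000 / 2.40 = 2,500 USD per patient. The last row depends on how the shortfall is generated. Another construction with the same correlation gave about 15,100, which corresponds to g = (6,000 − 15,100) / 4,000 = −2.3.

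With actual minus planned size, or with both sizes entered, the delay coefficient was about 6,000 (5,940 to 6,070) in these scenarios.

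**Set B.** 400 datasets of 100 trials. Planned size is lognormal (median 200, log-SD 0.8), delay has mean 12 and SD 10 months, shortfall has mean 20% and SD 25%, and noise has SD 100 thousand USD. Sites, country, intervention type and field are also in the model. Entries are the mean delay coefficient in thousand USD per month, with the share of negative estimates in brackets.

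| True value | Thousand USD per patient | Correlation 0.3 | Correlation 0.6 |
|---|---|---|---|
| 10 | 1 | 8.0 (0%) | 5.8 (0%) |
| 10 | 2 | 5.9 (0%) | 1.9 (20%) |
| 10 | 5 | −0.3 (51%) | −10.8 (100%) |
| 10 | 10 | −10.9 (87%) | −32.1 (100%) |
| 20 | 5 | 10.2 (4%) | −1.6 (57%) |

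The formula fits here too. In the 5-thousand row, g = (10 + 0.34) / 5 = 2.07 at correlation 0.3 and (10 + 10.77) / 5 = 4.15 at 0.6. These predict 10 − 2 × 2.07 = 5.9 and 10 − 2 × 4.15 = 1.7 for the 2-thousand row.

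At correlation 0 the mean was 10.1 (true 10, 5 thousand per patient). With delay and the size term only, again for a true 10 at 5 thousand per patient:

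- shortfall SD 10%: 5.1 at correlation 0.3 and 0.05 at 0.6;
- shortfall SD 25% and negative correlation: 20.7 at −0.3 and 31.2 at −0.6.

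With the shortfall in place of actual size, the coefficient was 10.04 and 9.97 where the planned model gave −0.3 and −10.8.

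**The case against.** **The direction is not known.** A reader might infer that the planned coefficient will be pulled towards or below zero because late trials usually under-recruit. The protocol does not say so. Its Background reports that many such trials stop early because of recruitment and organizational problems, but stopping early can leave a shortfall with little extension. A trial that extends until it reaches target has a delay and no shortfall. Both patterns move the correlation towards zero or below. This objection stands, and only a two-directional claim is supported.

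**Reversal needs particular inputs.** It requires a positive correlation and a per-patient cost that is high relative to the monthly cost of delay. With low per-patient costs the result is attenuation. This also stands.

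**Hypothesis (iii) does not rest on this model alone.** Objective C is exploratory, reasons reported by investigators are categorised, and planned and actual sample size are compared for each trial. A reader might infer that the hypothesis will therefore be answered wrongly, which goes too far. Yet none of these other analyses adjusts the effect of delay for enrolment.

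**The net effect of recruitment trouble, savings included, may be what is wanted.** That is a legitimate target, but conditioning on actual sample size does not deliver it. Nor does it isolate delay.

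**Other modelling choices.** The dollar scale suits an objective about excess costs, and the protocol proposes no R² criterion. Neither is a fault here.

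**Conclusion.** The point holds as a specification flaw: the stated covariate list leaves departure from planned enrolment unadjusted in a model of departure from planned cost. The bias in the delay coefficient is the per-patient cost times the extra patients missing per month of delay at a given actual size, with a minus sign. Under the assumptions shown, the result runs from no average bias through attenuation to a reversed sign in one direction, and to roughly two to two and a half times the true value in the other (11,400 to 15,100 against 6,000, at correlation −0.4). The protocol supplies none of the inputs that would fix where in this range the study will fall, so no single figure should be quoted as the expected bias. The case for action is that either error is possible and the remedy uses data already being collected.

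**What to change.** In the excess-cost model under Statistical analysis, replace actual sample size by actual minus planned sample size, or keep actual and add planned sample size. The first option costs no degrees of freedom and the second costs one. That is a small price even though trials without a budget drop out of this model ("for analyses in which initial budgets are considered we will conduct complete case analyses"). No new data are needed. A version on the relative scale (actual divided by planned) may be added as a sensitivity analysis; it was not tested here and is not needed to resolve the point.

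The same reasoning applies to number of sites, but a planned number of sites is not clearly among the listed variables, so no change is asked for there.
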